### Physical activity and sedentary behaviour measurements

#### ActiGraph GT3X+ Accelerometer

The ActiGraph GT3X+ is a small (4.6 cm × 3.3 cm × 1.5 cm) lightweight (19 g) tri-axial activity monitor that provides data on physical activity including activity counts, energy expenditure (kcal), steps and activity intensity (METs). The GT3X+ has an inclinometer to determine body position in sitting, lying and standing. The ActiGraph GT3X+ will be worn by participants for 24 h/day for seven days at each of the assessment time points. It will be attached to an elastic nylon strap which the participants can wear as a belt around the waist on the side of the affected knee. Participants will be asked to remove the ActiGraph when showering, bathing or swimming. After seven days of accelerometer wear, the accelerometers will be collected at the next possible visit to the hospital or arrangement will be made for collection from participants at a location most convenient to them.

The data will be downloaded and processed using a custom built SAS program (v 9.3, SAS Institute, Cary, NC, USA) that implements a series of decision rules with user-modifiable thresholds to automatically identify waking wear data for continuously worn ActiGraph GT3X+ of 60 s epoch vertical axis data. Non-wear time will be classified as one minute intervals with consecutive zero counts for a minimum of 90 min (with an allowance of up to 3 min of counts between 0 and 50). For the day to be classified as valid, a minimum wear time of 10 h (600 min) is required. Each 60 s epoch of accelerometry data is classified according to calibration equations as sedentary if <100 counts per minute (cpm) [57], light intensity activity if between 100 and 1951 cpm, moderate-vigorous intensity activity if between 1952 and 5724 cpm and vigorous if >5724 cpm [58]. Adjacent epochs within the same intensity will be grouped into bouts. Only participants with four or more valid days of wear (including at least one weekend day) will be included in the analyses. Total daily time spent in the different PA intensities will be obtained by totalling the duration of all the bouts at each level for each day. The values will then be normalised to total wear time and averaged over the number of valid days to derive an estimate of the mean time spent within each intensity. A break in sedentary time will be counted as one minute or more where the counts per minute is greater than 100.

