#### activPAL accelerometer

The activPAL is a small (2.0x1.4x0.3 in.) and light (20.1 g) single-unit accelerometer device worn on the mid-thigh fastened and secured by a non- allergenic adhesive tape and uses accelerometer-derived information about thigh position to estimate time spent in different body positions in lying, sitting and standing in 15 s epochs [44]. An activPAL will be taped to the thigh of the patient with waterproof taping and the patient will be asked to keep the activPAL on for the same amount of time as the ActiGraph. The activPAL can be covered with waterproof taping therefore, there will be no need to remove the activPAL when showering, bathing or swimming and therefore unless the device is reported to have fallen off by the patient, there will be no need for non-wear time classification for the activPAL data. The activPAL will be collected at the same time as the ActiGraph and data will be downloaded and analysed. The data are recorded in 15 s epochs and the manufacturer’s software will be used to determine the variables of interest from the downloaded activPAL data which will include the start time and duration of each sitting, lying, standing and stepping bout. Total sedentary time will be determined by summing the duration of all sitting/lying bouts. The interruption or break from sedentary time will be indicated at points where a sitting/lying bout is followed by a standing or stepping bout. Because the activPAL is worn for the same period as the ActiGraph, the same periods of sleep that are removed from the ActiGraph data, will also be removed from the activPAL data to be analysed. Further time-intensive methods of analysis will be employed according to current best practice guidelines [59].

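### The activPAL, which measures the primary sedentary outcome, gets no non-wear check unless the patient reports a fall-off, so unreported off-body waking time would most likely count as sedentary

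*Protocol article*

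**What the plan says.** Table 1 of the protocol article (Outcomes) assigns sedentary behaviour, a primary outcome, to the thigh-worn activPAL at 0, 1.5 and 6 months.

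The section on the activPAL accelerometer says that the device "uses accelerometer-derived information about thigh position to estimate time spent in different body positions". Because it is taped on with waterproof material, "there will be no need to remove the activPAL when showering, bathing or swimming". From this the section concludes that "unless the device is reported to have fallen off by the patient, there will be no need for non-wear time classification".

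The software output to be used is "the start time and duration of each sitting, lying, standing and stepping bout". The outcome is then defined: "Total sedentary time will be determined by summing the duration of all sitting/lying bouts". One thing is carried across from the other monitor: "the same periods of sleep that are removed from the ActiGraph data, will also be removed from the activPAL data to be analysed". The section ends with a general reference to further, time-intensive analysis under a cited best practice guideline.

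By contrast, the ActiGraph section has a non-wear rule (at least 90 min of consecutive zero counts, with a small allowance), a 600 min valid-day minimum, and a requirement of four or more valid days including a weekend day.

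**The concern.** The premise is narrower than the conclusion. Waterproof tape means that patients need not take the device off for water activities. It does not rule out tape that fails without the patient mentioning it, or a device deliberately taken off early. A report that the device fell off does not naturally cover deliberate removal.

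The outcome sums every sitting or lying bout, and the listed output has no off-body category. A motionless device lying flat would most plausibly be read as sitting or lying. Nothing else in the text clearly catches this. Only sleep periods are transferred from the ActiGraph, and the ActiGraph's wear criteria are defined on its own counts, so a patient who wears the belt but not the thigh monitor passes them. Dividing by wear time would not help, because the off-body time would count as both worn and sedentary.

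At stake is a primary outcome in which the trial wants to resolve a change of about 20 min/day.

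**Working it through.** **Inputs from the protocol article**
- Waking day 16 h = 960 min; target reduction 2 %, given as 20 min/day; N = 107; power 80 % (Sample size determination).
- Sedentary time in patients with OA, 9.8 h/day = 588 min (Background).
- Seven days of wear per time point (ActiGraph section).
- Significance level 0.05 (Data analyses).

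**Assumptions**
- Two-sided paired comparison with no allowance for attrition.
- A detached device is scored wholly as sitting or lying.
- The rates of unreported removal. The documents give none.

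**1. The plan's own figure.** 2 % of 960 min = 19.2 min, which the article rounds to 20. N = 107 cannot be reproduced, because the article gives no SD of the within-patient change. Solving backwards with the noncentral t distribution, 107 patients and 80 % power correspond to a standardised effect of 0.2733. The implied SD of change is 20 / 0.2733 = 73.2 min/day.

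**2. Effect on one patient.** Non-sedentary waking time is 960 − 588 = 372 min, or 38.75 % of the waking day. This is the part that would be misclassified.
- 4 waking hours off body: 240 × 0.3875 / 7 = 13.3 min/day on the 7-day mean.
- One lost waking day: 372 / 7 = 53.1 min/day.
- Three lost waking days: 3 × 372 / 7 = 159.4 min/day.
- Unreported waking non-wear in a week that produces a spurious 19.2 min/day: 19.2 × 7 / 0.3875 = 347 min, about 5.8 h.

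**3. Non-wear that differs between visits.** If the share of patients with one lost day is 10 percentage points higher at one visit than at another, the mean change shifts by 0.10 × 53.1 = 5.3 min/day, about a quarter of the target.

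**4. Equal non-wear at both visits.** The expected change is then unbiased, but noise is added. If a share q of visits, independently, carries an error e, then SD of change = √(73.2² + 2e²q(1 − q)).

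| Assumed scenario | e (min/day) | q | SD of change (min/day) | Power for 20 min, N = 107 |
|---|---|---|---|---|
| No unreported non-wear | 0 | 0 | 73.2 | 80 % |
| One lost day at 10 % of visits | 53.1 | 0.10 | 76.6 | 76 % |
| Three lost days at 5 % of visits | 159.4 | 0.05 | 88.1 | 64 % |

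**The case against.** The strongest reply is that this is a condensed article whose activPAL section ends by invoking best practice guidelines. On that reading, the rule only says that a zero-count algorithm like the ActiGraph's is unnecessary, and the cited guideline may contain a non-wear step. That is possible and cannot be checked here. But the closing sentence names no such step and does not withdraw the explicit rule. If the guideline does require one, the two statements conflict and the rule still needs correcting.

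Several limits stand:
- The documents do not say how a detached device is scored. One left upright could be read as standing, so a reader might infer a strictly one-directional error, but the text does not establish it.
- Off-body time inside an ActiGraph-defined sleep period is removed anyway.
- The report of a fall-off need not be spontaneous; patients could be asked when the devices are collected.
- The tape is described as non-allergenic, so skin reaction should not be presumed a frequent cause of removal.
- A reader might infer that time between the end of wear and collection, since "the accelerometers will be collected at the next possible visit to the hospital", also counts as sedentary. The text does not support this: wear is fixed at seven days, collection follows it, and the activPAL covers the same period as the ActiGraph. Nothing says that later recording is analysed.
- A reader might also infer that the estimated effect of TKA is biased. That needs non-wear to differ between visits, and the documents give no evidence of it.

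**Conclusion.** The concern holds in limited form. The article positively exempts the instrument for a primary outcome from non-wear classification on a reason that covers only one cause of non-wear. Followed as written, the rule lets unreported off-body waking time into the sedentary total.

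For an affected patient the error can be large: about 53 min/day from one lost waking day, more than two and a half times the 20 min/day target. For the cohort the size depends on frequencies that the documents do not give. In the two illustrations with equal rates at both visits the loss runs from about 4 to about 16 percentage points of power, and it rests on a back-solved SD as well as assumed rates. A demonstrated bias in the pre/post change, or a demonstrated loss of power, would be more than the documents support. The point should be corrected because the exposure is avoidable with data already being collected.

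**What to change.** Replace the statement that no non-wear classification is needed with a prespecified activPAL screen:

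1. Set to missing any waking activPAL sitting or lying bout during which the concurrently worn ActiGraph records sustained stepping or moderate counts.
2. Flag very long waking bouts without posture change for review. Do not delete them automatically: the ActiGraph's 90 min zero-count rule can itself label genuine still sitting as non-wear, so automatic deletion could bias sedentary time downwards.
3. Apply the plan's 10 h valid-day minimum to the activPAL data after the screen.
4. Report a sensitivity analysis without the screen.

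The cost is processing code and a few sentences of text, with no new data. The small downside is that some genuine long sitting may be queried, which the review step and the sensitivity analysis make visible.

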### Data analyses

Socioeconomic data will be summarised by descriptive statistics. Also, means and standard deviations will be used to summarise data for age, anthropometric (height, weight, BMI and %body fat), ActiGraph GT3X+ and ActivPAL.Scores for WOMAC, KOOS, OKS and KSS will be calculated by their respective scoring systems. Data will be analysed using SPSS v20 (SPSS Inc., Chicago, IL, USA).

Linear mixed models will be used to determine relationships between objectively measured habitual physical activity and sedentary behaviour, functional capacity and quality of life between pre-operative and 6 weeks and 6 months post-operatively. The model will be used to compare subjective measures of functional mobility (questionnaires) with objective measure of habitual physical activity. A multiple regression analysis will be used to describe the association between physical activity and/or sedentary behaviour, functional capacity and quality of life of OA patients before and after TKA. Also, a multiple regression will be used to determine the relationship between habitual physical activity and sedentary behaviour on anthropometric parameters of OA patients before and after TKA. A *p*-value of less than 0.05 will be considered significant.

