The objective assessment of habitual physical activity may provide an alternative method of assessing whether functional ability is improved in OA patients following TKA, as a change in activities of daily living (assessed using sedentary behaviour and light activity measurements) without a change in moderate to vigorous physical activity may correspond to a patient’s improved ability to function. Thus the aims of this study are to 1) describe habitual physical activity and sedentary behaviour patterns in knee OA patients scheduled for TKA, 2) to investigate the effects of unilateral primary TKA on objectively and subjectively measured habitual physical activity, sedentary behaviour and health outcomes of patients with knee OA and 3) to determine whether subjective measures of functional ability and sedentary behaviour (questionnaires) are correlated with objective measures of habitual physical activity and sedentary behaviour (accelerometry) before and after TKA. These data will help inform targeted interventions for the improvement and maintenance of physical activity.

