### Study design

This a longitudinal follow-up study of a cohort of participants who have been diagnosed with knee osteoarthritis and who are scheduled for TKA. After enrolment into the study, baseline assessments will be done prior to TKA. After TKA, participants will be followed-up and the same assessments done at baseline will also be done at six weeks, and six months post-operatively (Fig. 1). Habitual physical activity and sedentary behaviour will be measured using accelerometry (Actigraph GTX3+ and ActivPal monitors) at the specific time points. In addition, general health, functional ability, generic quality of life and pain questionnaires will be conducted at each time point on each participant.

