### Outcomes

All outcomes will be measured at baseline, six weeks after surgery and again six months after the surgical intervention (Table 1). The primary outcomes of this study will be an improvement habitual physical activity and a reduction in sedentary time after TKA. The secondary outcomes will be improvements in osteoarthritis-specific quality of life measures: Western Ontario and McMaster Universities Osteoarthritis Index (WOMAC), knee related quality of life from Knee injury and Osteoarthritis Outcome Score (KOOS), Knee Society Clinical Rating System (KSS), the Oxford Knee Score (OKS), self reported activity using the UCLA activity index; subjective pain scores, and self reported sleep quality.

**Table 1 Tab1:** Summary of outcome measures and respective collection method

Outcome	Variables	Measurement method	Time points (months)
Primary	Habitual physical activity	Accelerometry (ActiGraph worn on the hip)	0, 1.5, 6
	Sedentary behaviour	Accelerometry (activPAL worn on thigh)	0, 1.5, 6
Secondary	Knee OA-specific functional ability and quality of life	WOMAC	0, 1.5, 6
		KOOS	
		KSS	
		OKS	
	Activity	UCLA activity index	0, 1.5, 6
	Pain	VAS	0, 1.5, 6
	Sleep quality	Sleep questionnaire	0, 1.5, 6

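### Activity versus anthropometry is left to multiple regression although each patient is measured up to three times, and the function and quality-of-life regression duplicates the planned mixed model without a ranking

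*Protocol article*

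**What the plan says.** The design is a single cohort followed over time. Under Study design, "the same assessments done at baseline will also be done at six weeks, and six months post-operatively", and under Outcomes, "All outcomes will be measured at baseline, six weeks after surgery and again six months after the surgical intervention". Every patient can therefore supply three correlated records.

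The Data analyses section then names two kinds of method:

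- **Mixed models.** "Linear mixed models will be used to determine relationships between objectively measured habitual physical activity and sedentary behaviour, functional capacity and quality of life" across the pre-operative, six-week and six-month visits. The next sentence extends them to questionnaires against accelerometry: "The model will be used to compare subjective measures of functional mobility (questionnaires) with objective measure of habitual physical activity".
- **Multiple regression.** First, "A multiple regression analysis will be used to describe the association between physical activity and/or sedentary behaviour, functional capacity and quality of life" before and after surgery. Second, for the periods on both sides of the operation, "a multiple regression will be used to determine the relationship between habitual physical activity and sedentary behaviour on anthropometric parameters of OA patients before and" (sentence cut here).

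The section closes with one significance rule for everything: a p "value of less than 0.05 will be considered significant". It does not say whether the two regressions stack the visits or are run visit by visit. No mixed model is named for the anthropometric relation.

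**The concern.** Ordinary multiple regression assumes independent rows. The authors evidently know that these data call for a repeated-measures method, because they name one in the same section and then change method for two sets of associations.

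For anthropometry there is no other analysis to fall back on. The stated purpose there is to determine a relationship, not only to describe one, and BMI probably varies little within a patient over six months (an assumption). A near-constant predictor is where ignoring the clustering does most harm.

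For function and quality of life the problem is different. Two analyses address the same question, both fall under the same 0.05 rule, they can disagree, and nothing says which one prevails.

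**Working it through.** **Inputs from the article.** 107 participants (Sample size determination), 3 visits (Outcomes), significance level 0.05 (Data analyses; two-sided assumed). The article gives no within-patient correlations and no error rate for these regressions other than the nominal one. The figure of 107 was set for sedentary time and does not bear on this point.

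**Assumed inputs.** Exchangeable within-patient correlation rx for the predictor and ry for the outcome, no true association, visit means removed.

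**Reading 1: all visits pooled as independent rows** (up to 3 × 107 = 321). The variance of the slope is understated by the factor

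D = 1 + (m − 1) × rx × ry, with m = 3,

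and the actual error rate is 2 × [1 − Φ(1.96/√D)]. With rx = ry = 0, D = 1 and the formula returns the nominal 5 %.

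| rx | ry | D | 1.96/√D | Error rate |
|---|---|---|---|---|
| 0.3 | 0.3 | 1.18 | 1.80 | 7.1 % |
| 0.5 | 0.5 | 1.50 | 1.60 | 11.0 % |
| 0.7 | 0.7 | 1.98 | 1.39 | 16.4 % |
| 0.95 (BMI) | 0.5 | 1.95 | 1.40 | 16.0 % |
| 0.95 (BMI) | 0.7 | 2.33 | 1.28 | 19.9 % |

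Simulation with 107 patients and 3 visits (10,000 runs each) gave 7.1 %, 11.2 %, 16.4 %, 15.9 % and 20.1 % for the five rows. A separate simulation of the first three rows (8,000 runs each) gave 6.8 %, 11.0 % and 16.7 %. If only two visits were pooled (m = 2), the formula gives 8.0 % at correlation 0.5 in both variables (D = 1.25) and 12.6 % at 0.8 (D = 1.64).

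**Reading 2: one regression per visit.** Simulated error rate at a single visit: 4.7 % to 5.0 % at every correlation tried, so there is no inflation. The before and after slopes come from the same patients, however, and separate fits give no covariance between them. Their difference therefore has no valid standard error.

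**Mixed model on all three visits.** With a random intercept per patient, the simulated error rate was 4.9 % at correlation 0.5 and 5.5 % at 0.8 (1,500 runs each). A shorter run of 400 gave 4.8 % and 7.3 %, with a Monte Carlo standard error of √(0.05 × 0.95/400) = 1.1 percentage points. Taken together, the rate is close to nominal.

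**The case against.** The strongest reply is that nothing in the article says the visits are stacked. A regression for patients before and after surgery reads at least as naturally as one fit per time point, and then each p-value holds its 5 %. That stands. A reader might infer that the plan raises the false-positive rate to 11–20 %. The text does not support this, because it requires both the pooled reading and assumed correlations of about 0.5 or more.

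A reader might also infer that aim 3 rests on these regressions. It does not. That aim asks whether subjective measures "are correlated with objective measures of habitual physical activity and sedentary behaviour (accelerometry) before and after TKA", and the questionnaire-versus-accelerometry comparison is already given to the mixed model, as are the function and quality-of-life relationships. Nor does any aim explicitly ask whether an association changed after surgery, so the lack of such a test is a limitation and not a failure to meet an aim.

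It is also fair to say that anthropometry is in none of the three aims and is neither a primary nor a secondary outcome, and that a condensed article may leave modelling detail to a fuller plan. That lowers the importance. It does not remove the point, because the article names a method that does not by itself account for the repeated visits, and it names a second method for a question already assigned to the first.

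Lastly, a mixed model with a predictor that varies over time generally blends within-patient and between-patient associations unless they are separated. That also stands, and is one reason to keep a per-visit regression as description.

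**Conclusion.** The point holds in a narrow form. The anthropometric associations are assigned to multiple regression on repeatedly measured patients, with no statement of how the visits are handled and no mixed model as alternative. The function and quality-of-life regression duplicates the mixed model without a ranking.

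The consequence depends on an unstated choice. Pooling three visits would give an error rate of about 7 % to 20 % over the assumed correlations; fitting per visit keeps about 5 % but allows no formal before-and-after comparison of coefficients. The correlations are assumptions throughout.

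The primary outcomes and aim 3 are not affected. Severity is low.

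**What to change.** (a) Analyse the anthropometric associations with the linear mixed model already planned. Include visit, predictor and visit-by-predictor terms, and model the within-patient covariance over the three visits (participant random intercept or unstructured residual covariance). Read the visit-specific associations and their difference from that model, and state whether a between-patient or a within-patient association is meant.

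(b) Name the mixed model as the sole inferential analysis for function and quality of life. Drop the duplicate multiple regression, or keep it as a per-visit description without significance claims.

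The cost is a change of wording in the analysis section; data and software stay the same. The downside is somewhat wider intervals than a pooled regression would show, because the pooled ones ignore the repeated visits.
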